## 7 Statistical Plan

### 7.1 Sample Size Determination

#### Sample Size Estimation and Power Analysis for the Primary Aim of the Study

We established the sample size for the Primary Aim/Outcome/Hypothesis 1a (suicidal ideation over 10 days of acute sequential bilateral aTBS treatment) by incorporating a repeated measures design, with assumptions about potential participants (e.g., effect size/odds ratio), based on general guidance from a recent study that evaluated the effect of bilateral rTMS vs. sham stimulation on suicidal ideation in adult patients with treatment-resistant MDD. The results of the *a priori* sample size estimation and power analysis suggest that a sample size of 35 participants per group (N=70) achieves 80% power, at a 0.05 alpha level (two-tailed), to detect an overall odds ratio of 2.85 (sequential bilateral aTBS vs. Sham stimulation on lower-ordered intensity of suicidal ideation CSSR-S subscale scores—less suicidal ideation) in a 2 (between-subjects) group randomized design with 10 (within-subjects) repeated measurements of the primary ordinal outcome (suicidal ideation), when the proportion (or incident rate) of suicidal ideation from the sham group at the end of the 10-

day trial  $\geq 0.50$ , and the assumed within-subject correlation between observations (suicide ideation) on the same subject is  $\leq 0.50$  (0.50 was based on guidance from our preliminary TMS work). We note that the posited odds ratio of 2.85 for the current application is a bit more conservative than what was reported in the Weissman, et al. (2018) study of bilateral TMS vs. Sham stimulation on suicidal ideation in adult patients with treatment-resistant MDD (odds ratio=3.03).

We anticipate some dropouts (~10% based on treatment discontinuation results from our previous rTMS studies). Thus, ~80 participants will be enrolled to allow for this expected rate of attrition with the intent of capturing a range of evaluable data for 70 participants. The Power Analysis and Sample Size (PASS) 2019 software, version 14.0.15, was used to carry out the sample size and power analysis (PASS 2016, NCSS, Inc., Kaysville, Utah).

We recognize that to definitively evaluate the effect of sequential bilateral aTBS treatment on suicidal ideation in youth a sample size larger than 70 may be necessary. The treatment effect of sequential bilateral aTBS has not been previously studied in suicidal, depressed youth, we have no previous findings from a youth population to guide effect size selection for the present effort, and the current study would be the first of its kind to examine this treatment effect in depressed youth with suicidal ideation. The selection of 70 participants was, in part, resource-driven. The sample size is designed, in part, to detect a moderate effect and to establish a *proof of concept* so as to expand to a subsequent, larger-scale multi-center study. Nevertheless, the current proposal will permit an evaluation of whether receiving sequential bilateral aTBS shows initial evidence of an effect on improvement in suicidal ideation in a depressed adolescent population.

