**Figure 4. TMS improves suicidal ideation in adolescents with MDD**

trial of sequential bilateral aTBS for suicidal ideation in adolescents with MDD in the context of a clinical program. This study will recruit participants who are excluded from our prior and existing protocols. The research methodology will target and track suicidal ideation, which in adolescents is a pernicious public health problem with

underdeveloped interventions. This study follows an experimental medicine approach by evaluating a standard marker of cortical inhibition for baseline correlation with suicidal ideation severity and subsequent target engagement. The research team will also collect TMS-EEG measures of cortical inhibition to advance understanding of the neurophysiology of adolescent suicidality, develop additional reliable tools to probe cortical inhibition, and study GABAergic neuro-circuitry in adolescents.

**TBS treatment for Suicidal Ideation in Adolescents:** A prior study providing 30 sessions of open-label 10 Hz TMS for adolescents (N=19) with MDD examined suicidal ideation at baseline, after 10 treatments, after 20 treatments, and after 30 treatments. Outcome measures

of suicidal ideation were assessed with the Columbia Suicide Severity Rating Scale (C-SSRS) intensity of ideation subscale and item 13 (suicidality) on the Children's Depression Rating Scale Revised (CDRS-R). The predicted odds of suicidal ideation significantly decreased over 6 weeks of acute TMS treatment with both outcome measures (Figure 4). A more recent study provided 10 daily sessions of sequential bilateral TBS to depressed adolescents (N=20). Sequential bilateral TBS (at the dosing proposed in this application) was well tolerated in this sample of adolescents and demonstrated antidepressant effects. At baseline 17 of 20 of the subjects reported suicidal ideation with a mean C-SSRS intensity of ideation score of 3.11 and standard deviation (SD) of 1.45. After 10 daily sessions of sequential bilateral TBS, 9 subjects reported suicidal ideation with a mean C-SSRS suicidal ideation score of 2.11 (SD = 1.27).

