Table 3 describes the schedule of events. Table 4 describes all study assessments. The first visit is a screening visit. Informed consent and assent will be completed. A medical history, physical exam, vital signs, urine pregnancy test (if applicable) and urine drug screen will be completed. The subject's parent or guardian will not be told the results of the pregnancy test without the subject's permission. But if the study physician believes that being pregnant may cause serious health problems, they may need to tell the parent or guardian the test results. Patients with a positive urine drug screen that are not due to prescribed drugs are not eligible for study participation. The study physician will ask if the results can be shared with the parent or guardian. This information will be kept confidential if the subject chooses not to share the drug test results with the parent or guardian. The results of the urine drug test will not become part of the medical record, but the results will remain in the study record. Additional screening assessments include: the Transcranial Magnetic Stimulation Safety Screen (TASS), Antidepressant Treatment History Form (ATHF), pubertal development scale (PDS), Mini-International Neuropsychiatric Interview (MINI Kid for ages 12-17 and MINI for age 18), Young Mania Rating Scale (YMRS), Children's Depression Rating Scale Revised (CDRS-R), Columbia Suicide Severity Rating Scale (C-SSRS), Beck Depression Interview-II (BDI-2), Clinical Global Impressions Severity Scale (CGI-S), concurrent medications, adverse events, serious adverse events, demographics questionnaire, case report forms, and concurrent psychotherapy. The screening visit can occur on the same day or across 2 consecutive days based on participant preference.

## 6.2 Visit 2

After eligibility is confirmed, additional assessments will be completed (Table 3 and 4). These assessments include auditory thresholds, NIH Toolbox Cognition Battery, YMRS, CDRS-R, C-SSRS, BDI-2, Pre/Post Treatment Expectations CGI, concurrent medications, adverse events, serious adverse events, case report forms, concurrent psychotherapy. TMS neurophysiology measures are collected. The participant is randomized to the active aTBS group or sham aTBS. Coil localization (Beam F3) and motor threshold procedures are completed. The participant will complete day one of aTBS treatment (either 3 active sequential bilateral TBS or 3 bilateral sham treatments).

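### Section 7.1 claims 80% power for any sham ideation rate of 0.50 or more; its own calculation supports this only up to about 0.75, and it names the wrong C-SSRS subscale

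*Protocol*

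**What the plan says.** The sample-size text in Protocol Section 7.1 plans "a sample size of 35 participants per group (N=70") and says that this number "achieves 80% power, at a 0.05 alpha level (two-tailed), to detect an overall odds ratio of 2.85" in a two-group design with ten repeated measurements of the ordinal outcome. Two conditions are attached, each open at one end:

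- The "proportion (or incident rate) of suicidal ideation from the sham group at the end of the 10"-day trial is at least 0.50. No upper limit is given.
- The within-subject correlation is at most 0.50.

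The outcome in the power statement is described as "lower-ordered intensity of suicidal ideation CSSR-S subscale scores". The primary objective (Section 2.1), the primary endpoint (Section 3.2), Table 4 and the analysis of Hypothesis 1a (Section 7.2) all make the C-SSRS *severity* of ideation subscale the primary outcome. It is a five-point ordinal scale analysed by ordinal logistic GEE over the ten days.

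The inclusion criteria (Section 4.1) require a severity score of at least 1 at entry.

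**The concern.** A condition of 0.50 or more reads as a safe lower limit: the stated power is reached at 0.50, and a higher sham rate would do no harm. For a fixed odds ratio that is not so. As the sham rate approaches 1, the risk difference that corresponds to an odds ratio of 2.85 shrinks, and power falls with it.

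The high end is not remote here. Everyone has ideation at entry, and the test covers all ten treatment days. The stated condition concerns only the end of that period, so a trial could meet it and still have a much higher average sham rate.

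The subscale matters because the protocol uses both terms for C-SSRS data in Section 1.4. A reader of Section 7.1 cannot tell from the text alone which measure was powered.

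At stake is how a null result would be read in a pilot meant to inform larger studies: against an 80% figure stated more widely than its own calculation allows.

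**Working it through.** **Inputs, all from Section 7.1.** n = 35 per group; m = 10 measurements; correlation ρ = 0.50, the stated limit; OR = 2.85; two-sided α = 0.05 (z = 1.96); 80% power (z = 0.8416). The odds ratio is applied so that active treatment lowers the proportion with ideation.

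**Formulas.**

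- Variance factor for a mean of m exchangeable measurements: [1 + (m − 1)ρ]/m = (1 + 9 × 0.5)/10 = 0.55. Effective n = 35/0.55 = 63.6 per group.
- Active rate: p1 = odds/(1 + odds), with odds = [p0/(1 − p0)]/2.85.
- Required n per group = 0.55 × [1.96·√(2p̄(1 − p̄)) + 0.8416·√(p0(1 − p0) + p1(1 − p1))]² / (p0 − p1)², where p̄ is the mean of p0 and p1.
- Power = Φ{[(p0 − p1)·√63.6 − 1.96·√(2p̄(1 − p̄))] / √(p0(1 − p0) + p1(1 − p1))}.

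**The protocol's figure.** With p0 = 0.50, the odds are 1/2.85, so p1 = 0.260, p̄ = 0.380 and the difference is 0.240. The two square roots are 0.686 and 0.665.

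- n = 0.55 × (1.96 × 0.686 + 0.8416 × 0.665)²/0.2403² = 0.55 × 62.9 = 34.6, so 35 per group.
- Power = Φ[(1.917 − 1.345)/0.665] = Φ(0.86) = 80.5%.

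The stated sample size and power reproduce.

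**Same calculation, other sham rates within the stated range.**

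| Sham rate | Active rate at OR 2.85 | Difference | Power, 35 per group |
|---|---|---|---|
| 0.50 | 0.260 | 0.240 | 80.5% |
| 0.60 | 0.345 | 0.255 | 83.0% |
| 0.70 | 0.450 | 0.250 | 82.1% |
| 0.75 | 0.513 | 0.237 | 79.9% |
| 0.80 | 0.584 | 0.216 | 75.8% |
| 0.85 | 0.665 | 0.185 | 68.5% |
| 0.90 | 0.759 | 0.141 | 56.0% |
| 0.95 | 0.870 | 0.080 | 35.2% |

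Power is at least 80% from about 0.49 to 0.745. For 80% power, the odds ratio would have to be 3.00 at a sham rate of 0.80 and 3.79 at 0.90.

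**Sensitivity to the method.** A Wald test on the log odds ratio gives 78.7% at 0.50, 73.7% at 0.80 and 53.6% at 0.90. The pattern is the same.

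**End rate versus ten-day average.** The calculation uses one rate for all ten measurements, whereas the condition is on the end rate. The following paths are assumptions, evaluated with a binary GEE (independence working correlation, true correlation 0.50, OR 2.85 on every day):

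- Sham falling linearly from 0.80 to 0.50: 79.6%.
- From 0.95 to 0.50: 74.2%. An exchangeable working correlation gives 81.8% for this path.
- From 0.95 to 0.70, average (0.95 + 0.70)/2 = 0.825: 68.5%. This path meets the protocol's end-rate condition.

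**Subscale.** Section 7.1 says *intensity*; Sections 2.1, 3.2 and 7.2 and Table 4 say *severity*. No numerical input in Section 7.1 is specific to either.

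**The case against.** The strongest objection is that the primary analysis is ordinal. The losses at sham rates of 0.80 to 0.90 come from reducing the scale to ideation present or absent. A trial in which nearly everyone has some ideation can still separate the groups on how severe it is. With assumed category distributions and the same variance factor, Whitehead's ordinal formula gave about 84–91%, including cases with 90–95% of sham subjects having some ideation. It fell to about 76% when 70% of subjects were placed in one category. This stands, and it limits the point to the power statement as written. It does not rescue that statement, whose condition is on a proportion and which gives no category distribution.

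Second, a correlation below the limit would help: at 0.30, power is 90.2% at a sham rate of 0.80, but still 73.3% at 0.90. Third, the protocol calls itself a pilot, says a larger sample may be needed and describes N as partly resource-driven. That lowers the stakes. Fourth, the subscale mismatch may be only a naming slip; that is possible, since the inputs would not change.

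A reader might infer more than the documents support:

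- *That 80% holds only at a constant sham rate of 0.50.* The table shows otherwise, up to about 0.75.
- *That the full effect must be present from day 1.* Section 7.1 posits an overall odds ratio, so an effect that builds but averages 2.85 is covered. Power of about 35% (independence working correlation) arises only if 2.85 is taken as the day-10 value of an effect building from zero, which the protocol does not say.
- *That the 0.50 correlation is wrong.* The study cited for it "examined suicidal ideation at baseline, after 10 treatments, after 20 treatments, and after 30 treatments", not daily, which is a reason for caution. But 0.50 is a declared assumption and no document gives a daily correlation.
- *That 80% describes no realistic case.* It is met over part of the stated range and may be conservative for the ordinal model.

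**Conclusion.** The concern holds in a limited form. The sample-size arithmetic is correct at its own inputs, and 35 per group is reproduced. The error is in the range claimed for it: at the stated correlation limit, the binary calculation supports 80% only for ten-day average sham rates of about 0.50 to 0.75, and gives 75.8%, 68.5% and 56.0% at 0.80, 0.85 and 0.90. Universal ideation at entry makes the upper range plausible, although the protocol gives no sham trajectory and none can be fixed from it. Separately, the power statement contradicts the rest of the protocol on the primary subscale.

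This rests on reading the calculation as a time-averaged two-proportion test with exchangeable correlation, which reproduces the stated sample size. It does not show that the planned ordinal analysis is underpowered. The correction is worth making because it is cheap and concerns the figure against which the primary result will be read.

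**What to change.** Keep N and revise the text of Section 7.1:

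1. State that 80% power applies to an odds ratio of 2.85 averaged over the ten days, for ten-day average sham proportions of about 0.50 to 0.75 and a within-subject correlation of up to 0.50.
2. Either give the lower figures for sham rates of 0.80 to 0.90, noting that they come from the binary calculation and that the ordinal analysis may have more power, or restate the power on the ordinal severity scale with the assumed category distribution.
3. Replace *intensity* by *severity* in the power statement.

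The cost is a text amendment to one section, plus an ordinal power calculation if that option is taken. The downside is that the stated power becomes conditional and, under the binary calculation, less favourable.

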## 7.2 Statistical Methods

### Statistical Methods

All statistical analyses will be carried out using SAS software, version 9.4. The level of significance will be set at  $\alpha = 0.05$  (two-tailed) and, to address multiple testing (where applicable), p-values will be adjusted using the False Discovery Rate.

### Primary Aim

#### Data Analysis Plan for Primary Aim 1 (Hypotheses 1a–1c)

##### Primary Outcome for Aim 1: Suicidal Ideation during the 10-day acute Trial Period

**Hypothesis 1a:** We expect 10 days of sequential bilateral aTBS will have greater efficacy for improving suicidal ideation in adolescents with MDD (as assessed by the C-SSRS severity of ideation subscale) over the 10-day acute treatment trial compared to sham stimulation.

Suicidal Ideation (as measured by the C-SSRS severity of ideation subscale) over the 10-day acute sequential bilateral aTBS trial period will be the primary ordinal outcome measure. The acute change over time (10 days) in Suicidal Ideation will be compared between the two treatment groups (sequential bilateral aTBS vs. sham stimulation) using an ordinal logistic regression model within a Generalized Estimating Equation (GEE) framework. The logistic model will contain fixed effects terms for treatment, time, treatment  $\times$  time interaction along with baseline C-SSRS severity of ideation subscale as a covariate. Age, sex, pubertal status, antidepressant medication status, and depression severity (CDRS-R total as a time-varying covariate) will also be included as covariates in the model. Simple treatment group effects in each time period will also be assessed. [see sensitivity analysis section below for missing not at random (MNAR) mechanism].

##### Secondary Ordinal Outcome for Aim 1: Suicidal Ideation during the 12 month Follow-up

**Hypothesis 1b:** We expect that adolescents who receive 10 days of sequential bilateral aTBS will have lower suicidal ideation (as assessed by the C-SSRS severity of ideation subscale) over the 12-month follow-up period compared to sham stimulation.

Suicidal Ideation (as measured by C-SSRS severity of ideation subscale) will be assessed at monthly follow up visits over a 12-month period after the intervention. An ordinal logistic regression model within a GEE analysis framework similar to that described above for Hypothesis 1a will be used here to estimate suicidal ideation over the 12 month follow-up period. In addition to the covariates specified above in Hypothesis 1a, we will also consider the inclusion of pharmacotherapy and/or psychotherapeutic intervention received over the follow-up period as additional covariates.

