Please note that [name] works with a team of Board Certified Child and Adolescent Psychiatrists with expertise in adolescent depression, suicidality, severe psychiatric disorders in childhood, TMS protocols, and clinical research. One of these physicians (in the event [name] is away) or [name] is present in the treatment suite during TMS delivery and available 24 hours a day in the event of emergencies. We have standard operating procedures that the team of psychiatrists are comfortable with and have experience implementing. For example, this team collectively has had experience in hospitalizing suicidal research subjects. The overriding guiding principal for our research team is that subject safety is our central priority. Any decisions regarding clinical monitoring, referral for higher levels of treatment, and ongoing study participation are informed by what will optimize each subject's safety and clinical status. Beyond this, the Mayo Clinic Division of Child and Adolescent Psychiatry (11 board certified child and adolescent psychiatrists) always has an individual on call for psychiatric emergencies. While these colleagues are not co-investigators, they receive training on a regular basis regarding ongoing adolescent research efforts. All members of the Child and Adolescent Psychiatry Division have proficiency and comfort in dealing with psychiatric emergencies. They contact the PI ([name]) or the covering research child and adolescent psychiatrist with any emergency involving a research subject. Research subjects are ultimately offered standard of care interventions based on clinical presentation and need regardless of stage of participation (to include emergent evaluation in outpatient clinic, emergency medicine visits, or psychiatric hospitalization in Mayo Clinic, Generose 1-West, an 18 bed inpatient unit which is located directly below our neurostimulation treatment suite).

Other anticipated risks of TMS and TBS include dizziness, eye pain, facial numbness, facial pain, toothache pain, skin pain, facial muscle twitching, blurred vision.

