## 5.5 Prior and Concomitant Therapy

Reasonable efforts will be made to determine all somatic therapies for depression received by the participant in the past 2 years. All other medications and therapies received within six months of study enrollment will also be determined. All relevant information will be recorded on the Participants CRF. The ATHF will be completed to quantify treatment history.

During the trial, subjects will continue to take antidepressant medication if recommended by the referring clinician. Please note that subjects are not required to take an antidepressant medication for study participation for practical, ethical, and human subject protection concerns. Medication status and prior treatment resistance will be carefully recorded with the ATHF for relevant statistical considerations. The research team will collect information on subsequent pharmacological treatments during the 1-year follow up period.

Zaleplon, zolpidem, or zopiclone (1 dose nightly) as needed for treatment emergent insomnia or lorazepam (up to 2 mg daily) for treatment emergent anxiety, may be administered for up to 10 doses during the treatment phase of the study. The use of alternative hypnotics or anxiolytic compounds requires prior approval from the PI ([name]). Hormonal contraceptives are allowed. Short-term treatments for headaches, allergies, colds, and flu symptoms will be allowed during. All questions regarding the acceptability of specific medications must be approved by the PI/Sponsor ([name]).

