
**Concurrent Psychotherapeutic Sessions .** All subjects will receive psychotherapeutic treatment which meets and exceeds the local standard of care. This will consist of daily psychotherapeutic sessions during the 10-day course of sequential bilateral aTBS or sham treatment. The psychotherapeutic treatment protocol was adapted from prior NIMH funded work and a grant funded intensive outpatient program at UT Southwestern Medical Center Dallas. [name] (consultant) assisted in the proposed adaptation and will provide ongoing input to [name]. [name] will provide local supervision and oversight of the 10-day psychotherapy program. The research team will collect information on subsequent psychotherapy treatments during the 1-year follow up period.

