##### Secondary Count Outcome for Aim 1: Emergency Department visits and Hospitalization visits during the 12 month Follow-up

**Hypothesis 1c:** We expect that adolescents who receive 10 days of sequential bilateral aTBS will have fewer emergency department visits and fewer hospitalization visits related to suicidality during the 12-months after the intervention compared to sham stimulation.

Emergency department visits and hospitalization visits related to suicidality will be assessed at monthly follow up visits over a 12-month period after the intervention. A separate Poisson

(or negative binomial) mixed model analysis will be used to estimate the number of emergency department visits and hospitalization visits, respectively, over the 12 months after intervention for those who received sequential bilateral aTBS vs. those who received sham stimulation. The model will contain fixed effects terms for treatment, time, treatment  $\times$  time interaction, and the same covariates identified in hypotheses 1a and 1b above. Simple treatment group effects in each time period will also be assessed. Maximum likelihood estimation, Type 3 tests of fixed effects, and generalized least squares means will be used along with the best fitting covariance structure. The sandwich (robust covariance matrix) estimator will also be considered. The Poisson model will be checked for overdispersion. The Poisson (or negative binomial) regression will model the logarithm of each outcome as a random variable, and the mean and variance will be estimated on the logarithmic scale. Thus, to facilitate interpretation, geometric means will be reported, which will be obtained by exponentiating the log-scaled parameter estimates. The procedures of PROC GLIMMIX in SAS software will be used to conduct the Poisson (or negative binomial) regression for Hypothesis 1c and provide a robust mechanism for handling data that are assumed missing at random (see sensitivity analysis section below for MNAR).

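### The 12-month comparisons (1b and 1c) carry time-varying CDRS-R and may also carry care received after randomisation; with either covariate they do not estimate the total effect of assignment to aTBS

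*Protocol*

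**What the plan says.** Hypothesis 1b (Section 7.2) is a between-arm statement: aTBS recipients "will have lower suicidal ideation (as assessed by the C-SSRS severity of ideation subscale) over the 12-month follow-up period compared to sham stimulation". The model is the ordinal GEE of 1a. The covariate sentence opens "In addition to the covariates specified above in Hypothesis 1a" and continues "we will also consider the inclusion of pharmacotherapy and/or psychotherapeutic intervention received over the follow-up period as additional covariates".

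For 1c, the Poisson or negative binomial model contains treatment, time, their interaction "and the same covariates identified in hypotheses 1a and 1b above".

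The 1a list carried forward includes baseline C-SSRS, age, sex and pubertal status, and then: "antidepressant medication status, and depression severity (CDRS-R total as a time-varying covariate) will also be included as covariates in the model".

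The care in question is observed after treatment ends. Section 5.5: "The research team will collect information on subsequent pharmacological treatments during the 1-year follow up period". Section 6.3: "The research team will collect information on subsequent psychotherapy treatments during the 1-year follow up period". Section 1.5.2, under Suicidal Behavior, says how care is given: "Research subjects are ultimately offered standard of care interventions based on clinical presentation and need regardless of stage of participation".

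**The concern.** Medication and psychotherapy during follow-up are not fixed at baseline. An adolescent who worsens is likely to be given more care, so care in any month partly reflects earlier outcomes and, through them, the assigned arm. A model that conditions on it compares arms within groups formed after randomisation, and randomisation does not protect that comparison.

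Two forces then act on the estimate, in opposite directions:

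- Care stands in for past severity, so adjusting for it removes some of the treatment difference and shrinks the effect.
- If the care works and sham subjects receive more of it, the total effect is diluted by that compensation. Adjusting takes the dilution out and enlarges the effect.

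Neither result is the total effect that 1b and 1c ask about. In 1c the loop is tighter, because an admission may itself change therapy, and that therapy would then adjust the admission count. How care would be coded (by month, or over the whole follow-up) is not stated, and both codings have the problem.

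**Working it through.** **The plan's own figure.** The only stated sample size is for 1a: 35 per group, odds ratio 2.85, 80% power, two-sided 0.05, sham proportion 0.50, within-subject correlation 0.50, 10 measurements (Section 7.1).

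- Active proportion: 2.85 / (1 + 2.85) = 0.740.
- Two-proportion formula with pooled variance: [1.960 × √(2 × 0.620 × 0.380) + 0.842 × √(0.250 + 0.192)]² / 0.240² = 62.87 per arm.
- Repeated-measures factor: (1 + 9 × 0.5) / 10 = 0.55.
- 62.87 × 0.55 = 34.6, so 35 per arm, with power 80.5%. Dropout: 70 / 0.9 = 78, in line with about 80.

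The figure reproduces. It does not involve the 1b or 1c covariates, and no power is stated for those hypotheses.

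**Timing and dependence of the covariates.**

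- Follow-up care is post-randomisation by definition (Sections 5.5 and 6.3).
- Section 1.5.2 (Unimproved Depression or Clinical Deterioration) has depression and suicidality scales reviewed by a psychiatrist on the day they are given, including at monthly visits. Worsening leads to evaluation and, as indicated, a higher level of care.
- Section 8.5 calls the year naturalistic and expects suicide attempts and psychiatric hospitalisations to be common.
- CDRS-R is collected monthly in follow-up (Tables 3 and 4). Its item 13 rates suicidal ideation (Section 4.1), so it overlaps the outcome as well as being post-randomisation.

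**Illustrative size for follow-up care.** All rates here are assumptions.

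- Latent severity in each of 12 months = person effect (SD 1.5) − τ × arm − g × care + logistic error.
- Probability of care = expit(−0.5 + k × previous month's severity).
- Severity was cut into ordered levels and fitted by a pooled cumulative-logit model, with and without care as a covariate. The change is ln(adjusted OR) / ln(unadjusted OR) − 1.

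| τ | g (care benefit) | k (trigger) | Care, sham / active | OR without care | OR with care | Change in log OR |
|---|---|---|---|---|---|---|
| 1.5 | 0 | 0 | 0.38 / 0.38 | 3.00 | 3.00 | 0.0% |
| 1.5 | 0 | 0.5 | 0.40 / 0.27 | 3.02 | 2.82 | −6.0% |
| 1.5 | 0 | 1 | 0.43 / 0.24 | 3.04 | 2.63 | −12.8% |
| 1.5 | 0.5 | 0.5 | 0.38 / 0.26 | 2.93 | 2.84 | −2.8% |
| 1.5 | 0.5 | 1 | 0.40 / 0.23 | 2.87 | 2.64 | −7.8% |
| 1.5 | 1 | 0.5 | 0.37 / 0.26 | 2.71 | 2.74 | +1.2% |
| 1.5 | 1 | 1 | 0.38 / 0.22 | 2.75 | 2.69 | −2.1% |
| 1.05 | 2 | 0.5 | 0.34 / 0.27 | 1.83 | 2.01 | +14.9% |
| 1.05 | 2 | 1 | 0.35 / 0.24 | 1.86 | 2.03 | +13.9% |
| 1.05 | 2 | 0 | 0.37 / 0.38 | 2.07 | 2.21 | +8.8% |

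The rows with τ = 1.5 use 20,000 simulated subjects and those with τ = 1.05 use 6,000.

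The last row has care independent of severity. Its shift is non-collapsibility of the odds ratio: on the linear latent scale the effect barely moves (1.092 to 1.082). In the two rows above it the latent-scale change is +10.5% (0.847 to 0.936) and +11.5% (0.845 to 0.942), so most of the increase there is not an artefact of the odds-ratio scale.

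With τ = 0 (12 settings of g and k) the odds ratio changed by at most 0.011.

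No calculation was made for the 1c count models or for time-varying CDRS-R. Those parts rest on the reasoning above.

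**The case against.** The strongest reply is that the 1b sentence commits to nothing. It leaves inclusion of follow-up care open, and 1c inherits an optional item. A reader might infer that both 12-month models will be adjusted for care; the text does not support that for 1b, and for 1c it is unclear. This stands as a limit on the wording. It does not clear the plan: the protocol names these covariates, gives no rule for using them and names no baseline-only model as the main one. Time-varying CDRS-R is not optional.

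A reader might also infer that adjustment must pull the estimate toward no difference. The table contradicts this: strongly effective care moves it the other way.

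That follow-up care responds to suicidality is partly inference. The statement on care by need comes from text on psychiatric emergencies, and some medication may simply continue what was taken at entry (Section 5.5). The review of scales at monthly visits supports the link, but the protocol does not say why each therapy is given.

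The size may be modest. On the 1a planning inputs the log odds ratio is ln 2.85 = 1.047, with implied standard error 1.047 / (1.960 + 0.842) = 0.374. A 12.8% shift is 0.134, about 0.36 of a standard error. That is fair as a scale, but it borrows 1a precision for outcomes that have no stated power.

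Finally, in a naturalistic follow-up a model that accounts for later care can be informative. That is right, provided it is labelled supplementary.

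**Conclusion.** The point holds in conditional form. If follow-up pharmacotherapy or psychotherapy enters the 1b or 1c models, those models do not estimate the total effect of assignment. Time-varying CDRS-R already creates the same problem in both, with the added difficulty that the scale contains a suicidal-ideation item.

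For follow-up care, the distortion was about −13% to +15% on the log odds ratio scale, part of the upper end being non-collapsibility. These figures assume care rates, triggers and benefits that the protocol does not give. The distortion needs care that responds to severity and a treatment effect on severity or on care. With no treatment effect it is near zero, so this does not show that the plan would produce false positive findings.

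A reader might infer that the primary result is compromised. The follow-up-care sentence does not touch the 10-day analysis, and 1b and 1c are labelled secondary outcomes of Aim 1. The CDRS-R term is also in the 1a model, but that is a separate question not worked here. The planned 70 evaluable and about 80 enrolled stand.

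**What to change.** In Section 7.2:

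- **1b:** replace the covariate sentence with a statement that the main model uses only pre-randomisation covariates: baseline C-SSRS severity of ideation, age, sex, pubertal status, baseline antidepressant status and baseline CDRS-R total.
- **1c:** list the same covariates explicitly instead of referring back to 1a and 1b.
- **Follow-up care:** report pharmacotherapy and psychotherapy received during the 12 months by arm. Label any model that adjusts for this care, or for time-varying CDRS-R, as supplementary and not as the estimate of the effect of assignment.

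The cost is a few sentences. The baseline measures are already collected before randomisation (Section 6.2, Table 3) and follow-up care is already recorded, so data collection, sample size and study conduct do not change.
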